### Sample size

The sample size calculation is based on a clinically relevant difference between treatment groups with 80% power and a 5% significance level. Considering that the minimal detectable change of the ARAT (primary outcome) is 5.7 points and that an acceptable difference between groups of 15% is defined to be clinically meaningful [84, 85], a sample size of 26 participants will be required in each group. From experience gathered in previous studies [32, 77], the dropout rate in this type of interventions is relatively low (15%). Taking this rate into consideration, a final estimation of 60 participants is needed in the study, 30 per group.

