#### Primary outcome

The primary outcome will be upper extremity function measured with the *Action Research Arm Test* (ARAT, [46]). The ARAT is recommended for use in chronic stroke and outpatient rehabilitation by the StrokeEDGE Task Force Group [81] and has excellent test-retest and inter/intra-rater reliability [69, 85]. The measure is a 19-item test divided into four subtests (grasp, grip, pinch and gross movement). For each item, the patient is asked to perform a simple task that involves a functional movement of the affected upper limb. Each task is rated using a 4-point ordinal scale. The maximum possible score is 57 and the minimal clinically important difference is 5.7 points [84].

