### Data analysis

Statistical analysis will be performed using *R* (R Core Team, 2019) and the *Statistical Package for the Social Sciences* (SPSS version 21, SPSS inc., Chicago, Illinois, USA). For descriptive analyses, quantitative data will be analysed using mean and standard deviation if the data is normally distributed and median and interquartile range will be used for variables that are not normally distributed. Qualitative variables will be presented using frequency distributions and percentages.

An intention-to-treat analysis will be performed for all outcome variables including all patients that were assigned to a group and for whom the primary outcome was collected at baseline. In the case of participants that withdraw form the study, the score at baseline will be assigned for all the evaluation points and reasons for withdrawal will be reported.

The effect of the intervention on the primary outcome, the ARAT, will be assessed using the chi-square test. Taking into account the minimal clinically important difference of this test (5.7 points) data will be dichotomized into two categories: *clinically improved* or *unchanged/deteriorated.* An analysis of covariance (ANCOVA) will be carried out for all secondary outcomes to determine differences between groups across time using demographical and clinical baseline variables as covariates. The level of significance will be set at *p* < 0.05 for all statistical tests and corrected for multiple comparisons when necessary.

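### The claimed 80% power with 26 per group does not hold for the planned chi-square test: about 18-40% if the 15% is a responder difference, at most about 61% if 26 came from a comparison of means

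*Protocol article*

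**What the plan says.** Protocol article, Sample size: "The sample size calculation is based on a clinically relevant difference between treatment groups with 80% power and a 5% significance level". The section then offers two figures. The first is that "the minimal detectable change of the ARAT (primary outcome) is 5.7 points". The second figure, and the number per arm drawn from both, read: "an acceptable difference between groups of 15% is defined to be clinically meaningful [84, 85], a sample size of 26 participants will be required". After a 15% dropout allowance, "a final estimation of 60 participants is needed in the study, 30 per group". The section does not say whether the 15% is a difference in responder percentages or in scores, and it names no test.

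Protocol article, Data analysis: "The effect of the intervention on the primary outcome, the ARAT, will be assessed using the chi-square test". Each participant is classed as improved or not improved using a cut of 5.7 points. Participants who withdraw are given their baseline score at every later visit, so they stay in the analysis as unchanged.

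Protocol article, Primary outcome: "The maximum possible score is 57 and the minimal clinically important difference is 5.7 points".

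**The concern.** A power statement belongs to a particular test and a particular effect. Here the test is a comparison of two proportions with 26 to 30 patients per arm. For such a test a 15-point difference is small, and 26 per arm looks far too few.

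What is at stake is how a null result is read. The comparator, GRASP, is an active programme that the protocol describes as effective, so a non-significant result is a realistic outcome. A reader who trusts the 80% figure would take it as evidence against a 15% advantage for eMST. If the real power is 18-40%, the test would miss such an advantage 60-82% of the time.

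**Working it through.** **Inputs from the protocol.** Power 80%, significance 5% (two-sided assumed), difference 15%, 26 per group, 30 per group after dropout, 15% dropout (Sample size); chi-square on a binary endpoint cut at 5.7 points, withdrawals counted as unchanged (Data analysis); ARAT maximum 57 (Primary outcome). **Assumed:** the control responder rate, varied because none is stated.

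**Step 1. Try to reproduce 26 as a responder calculation.** With p1 and p2 the responder rates and p̄ their mean,

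n per group = [1.960·√(2p̄(1−p̄)) + 0.842·√(p1(1−p1) + p2(1−p2))]² / (p2 − p1)².

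Example, 20% vs 35%: p̄ = 0.275. The first term is 1.960 × √0.39875 = 1.238 and the second is 0.842 × √0.3875 = 0.524. Their sum squared is 3.103, and 3.103 / 0.0225 = 137.9, so 138 per group.

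The power columns come from exact binomial enumeration of the uncorrected chi-square, with all patients observed.

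| Control vs eMST responders | n per group for 80% | Exact power, n = 26 | Exact power, n = 30 |
|---|---|---|---|
| 0% vs 15% | 48 | 56% | 68% |
| 5% vs 20% | 76 | 40% | 45% |
| 10% vs 25% | 100 | 31% | 34% |
| 20% vs 35% | 138 | 24% | 25% |
| 30% vs 45% | 163 | 21% | 22% |
| 42.5% vs 57.5% | 174 | 18% | 22% |
| 60% vs 75% | 152 | 22% | 23% |
| 80% vs 95% | 76 | 40% | 45% |

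No control rate gives 26. The minimum is 48 two-sided and 38 one-sided. A Yates correction lowers power at n = 26 to about 12-17% for control rates of 5-50%.

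**Step 2. What 26 and 30 per group can detect.** The table gives the smallest responder difference with 80% exact power, rounded up to a whole percentage point.

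| Control rate | n = 26 | n = 30 |
|---|---|---|
| 5% | 28 points | 26 points |
| 10% | 33 | 31 |
| 20% | 37 | 35 |
| 30% | 39 | 36 |
| 50% | 35 | 34 |

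**Step 3. Withdrawals counted as unchanged.** With 15% withdrawal in both arms, each responder rate is multiplied by 0.85 and 30 per group are analysed. For example, 20% vs 35% becomes 17.0% vs 29.75%, with exact power of 21%. Over control rates of 5-80% the range is about 17-39%.

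**Step 4. Try to reproduce 26 as a comparison of means.** A two-sided t-test with 26 per group has 80% power at a standardised difference of 0.792. The SD that yields 26 is therefore 5.7 / 0.792 = 7.2 if the difference is 5.7 points. If 15% means a share of the scale (0.15 × 57 = 8.55 points), it is 8.55 / 0.792 = 10.8. Neither SD is in the protocol.

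Suppose one of these SDs were right and change scores were normal. Dichotomising at 5.7 points turns the mean difference into two responder rates. The control mean most favourable to the test gives, for example, 46.7% vs 76.1%. Exact chi-square power at n = 26 is then about 61% at most.

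**The case against.** The strongest reply is that the 15% has no stated scale, so 18-40% is the result of one reading and not a fact about the protocol. That stands. The range needs two assumptions: that 15% means percentage points of responders, and that the control rate lies between 5% and 80%. Outside those rates power is higher: 48% at a 2% control rate and 56% at 0%. The reply does not rescue the claim, because 80% is not reached at 26 per group under any control rate, nor under the means reading once the planned test is applied.

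A second reply is that a journal article condenses the full protocol, so an unprinted SD or control rate is not a fault in itself. That also stands. A two-sided t-test for a standardised effect of 0.8 needs 25.5, rounded up to 26, so a means calculation may lie behind the figure. The complaint is the mismatch between the printed power and the printed test, which no further document can remove.

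Some stronger inferences are tempting and should not be drawn:

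- **That 5.7 points (10% of 57) contradicts 15%.** If 5.7 is the individual responder cut-off and 15% the between-group difference in responders, they are different quantities.
- **That the dropout step undermines the design.** 26 / 0.85 = 30.6 would round up to 31, against the stated 30, a difference of one patient per arm. Counting only completers as analysed also overlooks that withdrawals stay in the denominator.
- **That calling 5.7 a minimal detectable change in one section and a minimal clinically important difference in others changes the result.** The number is the same, so this is editorial.

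**Conclusion.** The point holds. The stated 80% power is wrong for the primary test as planned. Read as a responder difference, 15 points has about 18-40% exact two-sided power at 26 per group for assumed control rates of 5-80%, and about 56% at best. It would need about 76-174 per group, or 48 at the most favourable extreme. With 30 per group and 15% withdrawal counted as unchanged, the range is about 17-39%. Read as a mean difference, 26 depends on an unstated SD, and the dichotomised test reaches at most about 61%. That last figure assumes normal change scores, which is only approximate for a bounded ordinal sum such as the ARAT.

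The documents do not settle which reading was meant, and the conclusion does not depend on the choice. Nor does it follow that the trial must enrol more patients: the error lies in what the present size is said to achieve.

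**What to change.** Rewrite the Sample size paragraph for the test actually used, by one of two routes.

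1. **Keep the chi-square.** State that the 15% is an absolute difference in responders and give the assumed control rate. Say that 26 per group gives 80% power only for a difference of about 28-39 percentage points (control rates 5-50%), or about 26-36 points with 30 per group all observed. Say also that power for 15 points is about 18-40% with 26 per group. Add that withdrawals are analysed as unchanged, so with 15% withdrawal in both arms power for 15 points at 30 per group is about 17-39% (control rates 5-80%). The cost is rewording and a less favourable power statement.

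2. **If a mean difference was intended,** say so. Give that difference and an SD from a cited source, and make a baseline-adjusted comparison of ARAT scores the primary analysis. The SD should not be solved backwards from 26. This costs more: it changes the primary analysis of a registered trial and needs a documented amendment, made before outcome data are seen by group.

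Under either route, use one label for 5.7 points throughout. Enrolment can stay at 60.

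### The drop-out allowance assumes that withdrawals leave the analysis, but the analysis plan keeps them as unchanged, so 30 per group does not preserve the stated 80% power

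*Protocol article*

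**What the plan says.** The Sample size section of the protocol article plans the trial "with 80% power and a 5% significance level" and states that "a sample size of 26 participants will be required in each group". It then cites a 15% drop-out rate from earlier studies and reaches the final figure: "a final estimation of 60 participants is needed in the study, 30 per group".

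The Data analysis section defines the intention-to-treat analysis as "including all patients that were assigned to a group and for whom the primary outcome was collected at baseline". For patients who withdraw, "the score at baseline will be assigned for all the evaluation points". The primary analysis is a chi-square test on ARAT change, split at 5.7 points into clinically improved versus unchanged or deteriorated.

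**The concern.** The two sections describe different analyses. Raising 26 to 30 so that about 26 remain after drop-out treats drop-outs as lost from the test. Under the Data analysis section nobody with a baseline ARAT is lost. A patient who withdraws has a change of zero by rule, falls below the 5.7-point threshold and stays in the denominator as a non-improver.

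Losing patients reduces the sample size. Scoring them as non-improvers reduces the effect. Required sample size varies roughly with the inverse square of the effect, so an allowance that only replaces lost patients is too small. At stake is whether the stated 80% describes the primary test that will actually be run.

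**Working it through.** **Inputs.** From the Sample size section: 80% power, 5% significance, 26 per group, 15% drop-out, 30 per group. From the Data analysis section: all assigned patients with a baseline ARAT are analysed, withdrawals get their baseline score, and the test is a chi-square on improved versus not. Assumed, because the document does not give them: a two-sided test, equal drop-out in both arms, completers improving at the planned rates, and the control improvement rate.

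**1. The plan's own figure.** 26/(1 − 0.15) = 30.6, so 31 per group (62 in total). The stated 30 agrees with 26 × 1.15 = 29.9. With 30 per group, 30 × 0.85 = 25.5 completers are expected. If drop-outs did leave the analysis and 26 gave 80%, then 25.5 would give 79.2%. The rounding therefore costs about 1 point.

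**2. What the baseline-score rule does.** If completers improve at rates p1 (control) and p2 (eMST), and a share d in each arm is scored as not improved, the analysed rates are (1 − d)p1 and (1 − d)p2. With d = 0.15 the difference becomes 0.85(p2 − p1), with all 30 per group analysed.

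**3. Power of the planned test.** For each assumed p1, p2 is set so that 26 per group gives exactly 80%. Both rates are then multiplied by 0.85 and power is computed at n = 30:

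power = Φ{ [ (p2 − p1)√n − 1.96√(2p̄(1 − p̄)) ] / √(p1(1 − p1) + p2(1 − p2)) }, where p̄ is the mean of the two rates.

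Example, control rate 20%. At 26 per group, 80% power needs p2 = 57.0%. The diluted rates are 17.0% and 48.45%, a difference of 0.3145, with p̄ = 0.327. The numerator is 0.3145 × √30 − 1.96 × 0.664 = 1.723 − 1.301 = 0.422. The denominator is √(0.141 + 0.250) = 0.625. The ratio is 0.675 and the power about 75%.

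| Control rate | eMST rate for 80% at 26 | Rates × 0.85 | Power at 30 (formula) | Power at 30 (exact) | n per group for 80% (formula) |
|---|---|---|---|---|---|
| 5% | 35.5% | 4.3 / 30.2% | 77% | 77% | 33 |
| 10% | 43.7% | 8.5 / 37.1% | 77% | 75% | 33 |
| 20% | 57.0% | 17.0 / 48.5% | 75% | 74% | 34 |
| 30% | 68.0% | 25.5 / 57.8% | 73% | 75% | 36 |
| 40% | 77.4% | 34.0 / 65.8% | 70% | 71% | 38 |
| 50% | 85.5% | 42.5 / 72.7% | 67% | 65% | 41 |
| 60% | 92.4% | 51.0 / 78.5% | 61% | 58% | 47 |

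The exact column enumerates the chi-square test and has its own calibration to 80% at 26, so its eMST rates differ slightly from those shown. Its uneven steps come from discreteness. With a control rate near zero, power is still about 78%.

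**4. Correct rounding does not repair it.** At 31 per group the formula gives 78.6% (control 5%), 76.3% (20%), 71.7% (40%) and 62.6% (60%).

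**5. Cross-check on means.** This is not the planned test, but it shows the mechanism. The standardised effect giving 80% at 26 per group is (1.96 + 0.842) × √(2/26) = 0.777. At 30 per group without dilution, power is 85.3%. With 0.85 × 0.777 = 0.660 and the SD held fixed, 0.660 × √(30/2) − 1.96 = 0.60, a power of 72.5%. Restoring 80% takes 26/0.85² = 36 per group.

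**The case against.** **The 26 is itself unsupported.** This stands. The section defines the target as "an acceptable difference between groups of 15% is defined to be clinically meaningful" but gives no SD, control rate or scale. Read as 15 percentage points improved, no pair of rates gives 26: at least 48 per group are needed two-sided and 38 one-sided. The scenarios above need differences of about 30 to 38 points, roughly twice the stated 15. They show what the drop-out handling does to a design that starts at 80%, and they do not endorse the 26. The missing basis for 26 is a separate and larger problem.

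**The planned effect might already count drop-outs as non-improvers.** Then 26 would need no allowance, and 30 per group would exceed 80%. The document does not say so, and adding patients for drop-out indicates that 26 is meant as a number of completers. Even on that reading, the allowance does not match the analysis.

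**The single factor 0.85 is an assumption.** This also stands. It needs equal drop-out and completers who improve at the planned rates. In general the analysed difference is (1 − d2)p2 − (1 − d1)p1, so higher drop-out under eMST would shrink it further and higher drop-out under control would shrink it less.

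**Stronger readings that a reader might infer.** One is that the trial's true power is some particular figure in the low to mid 70s. The documents do not support this, since every figure depends on an undocumented control rate and on accepting 26, and they give no reason to stop at a 40% control rate. Another is that the shortfall comes from miscalculated inflation; that slip is one patient per group. A third is that the baseline-score rule is wrong. Counting withdrawals as non-improvers in a responder analysis is a recognised, prespecified choice. The fault lies in the mismatch with the sample-size paragraph.

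**Conclusion.** The inconsistency is real and is visible in the document without any outside figure: the allowance treats drop-outs as removed, and the analysis keeps them as unchanged. Taking 26 per group as the number of completers that gives 80%, power at 30 per group is below 80% at every control rate tried. On the exact test it is about 71-77% for assumed control rates of 5-40% and about 58-65% at 50-60%. The direction does not depend on the control rate, but the size does. All figures assume a two-sided 5% test, 15% drop-out in each arm and completers improving at the planned rates. The difference between 30 and 31 per group is minor.

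**What to change.** In the Sample size section, replace the bare 80% with the power of the planned chi-square test at 30 per group under the 15% drop-out and the baseline-score rule. State the control and eMST improvement rates assumed and show power over a plausible range of control rates. The conditional figures given here should not be copied in as the trial's power, because they presuppose the 26.

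If the sponsor prefers another method for withdrawals, power should be quoted for that analysis instead. That choice is a trade-off and is not required by this point.

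The cost is a revised paragraph and a short calculation. No extra recruitment is needed. The stated power will probably be less favourable.

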### Data analysis

Statistical analysis will be performed using *R* (R Core Team, 2019) and the *Statistical Package for the Social Sciences* (SPSS version 21, SPSS inc., Chicago, Illinois, USA). For descriptive analyses, quantitative data will be analysed using mean and standard deviation if the data is normally distributed and median and interquartile range will be used for variables that are not normally distributed. Qualitative variables will be presented using frequency distributions and percentages.

An intention-to-treat analysis will be performed for all outcome variables including all patients that were assigned to a group and for whom the primary outcome was collected at baseline. In the case of participants that withdraw form the study, the score at baseline will be assigned for all the evaluation points and reasons for withdrawal will be reported.

The effect of the intervention on the primary outcome, the ARAT, will be assessed using the chi-square test. Taking into account the minimal clinically important difference of this test (5.7 points) data will be dichotomized into two categories: *clinically improved* or *unchanged/deteriorated.* An analysis of covariance (ANCOVA) will be carried out for all secondary outcomes to determine differences between groups across time using demographical and clinical baseline variables as covariates. The level of significance will be set at *p* < 0.05 for all statistical tests and corrected for multiple comparisons when necessary.

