**Fig. 1 Fig1:**
[figure not shown]
Study design. This study is a parallel-randomised controlled trial with two treatment groups (enriched Music-supported Therapy group [eMST-group, *n* = 30] and Control group [CT-group, *n* = 30]). Participants will be evaluated before and after the intervention as well as in a 3-month follow up

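### Giving every withdrawer the baseline score at all visits can discard observed post-intervention data, fixes the patient as not improved on the primary endpoint, and biases the comparison if drop-out is unequal and withdrawers would have improved

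*Protocol article*

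**What the plan says.** The Data analysis section defines the population: "An intention-to-treat analysis will be performed for all outcome variables including all patients that were assigned to a group", provided that the primary outcome was collected at baseline. It then fixes how withdrawals are handled: "In the case of participants that withdraw form the study, the score at baseline will be assigned for all the evaluation points". The sentence makes no exception for scores collected before withdrawal, and the article gives no other missing-data method.

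On visits, the caption of Fig. 1 says: "Participants will be evaluated before and after the intervention as well as in a 3-month follow up".

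On the primary analysis, the plan says: "The effect of the intervention on the primary outcome, the ARAT, will be assessed using the chi-square test". At a threshold of 5.7 points, "data will be dichotomized into two categories: *clinically improved* or *unchanged/deteriorated". For the rest: "An analysis of covariance (ANCOVA) will be carried out for all secondary outcomes to determine differences between groups across time". The intention-to-treat sentence covers all outcome variables, so the baseline rule reaches the secondary outcomes as well.

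The Sample size section plans 26 per group "with 80% power and a 5% significance level", expects 15% drop-out overall, and recruits 30 per group. It gives no drop-out by arm.

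**The concern.** Two things follow from the wording.

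First, a patient who completes the 10 weeks, is measured at post-intervention and then leaves before the 3-month visit has withdrawn. Taken at its word, the rule puts the baseline score at both later visits, so a measured result is lost.

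Second, a patient given the baseline score has a change of zero and can never reach 5.7 points. For every withdrawer the rule, not a measurement, decides the primary result.

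Assigning zero change is often defended as cautious. That defence is weaker here because the Study design section describes the control programme as validated and effective in chronic stroke. If both arms improve, zero change penalises whichever arm loses more patients. Unequal loss is plausible, though not documented: one arm has an app, instruments and a scheduled weekly online group, and the other a booklet and a weekly phone call. At stake are the estimate and error rate of the primary comparison. The secondary ANCOVAs are also affected, since they would treat assigned zero changes as measured data.

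**Working it through.** **Inputs from the article.** 30 per arm; 15% drop-out overall; responder threshold 5.7 ARAT points; 5% significance level.

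**Assumed, because the article does not give them.** Response rate p from 30% to 70%; the split of drop-out by arm; withdrawers respond like completers; for power only, an SD of change of 7.2 points and a control gain of 0 to 5.7 points. Tests are two-sided, chi-square without continuity correction.

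**The plan's own drop-out step.** 26 × 1.15 = 29.9, which gives the stated 30 per group. The usual form, 26 / 0.85 = 30.6, gives 31. The difference is immaterial to this point.

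**How many patients the rule decides.** 0.15 × 60 = 9. If one third to one half of them left after post-testing (assumption), 3 to 4.5 patients would have an observed post score replaced. Of these, 3 × 0.3 = 0.9 to 4.5 × 0.7 = 3.15 would have been measured as improved.

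**Bias on the responder scale.** Let d be the drop-out proportion in an arm, p the response rate of completers and q the rate that withdrawers would have had. The full-information rate is (1 − d)p + dq, and the rule reports (1 − d)p. Each arm is lowered by dq, so the bias in (eMST − control) is d_C·q_C − d_E·q_E. It is zero if withdrawers would not have responded (q = 0).

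**No true difference, q = p in both arms.** The false difference is p(d_C − d_E). The rejection rate is that of the chi-square test at 30 per arm with rates p(1 − d_E) and p(1 − d_C).

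| Drop-out, eMST / control | p | False difference (points) | Type I error |
|---|---|---|---|
| 15% / 15% | 0.3, 0.5, 0.7 | 0 | about 5% |
| 10% / 20% | 0.3 | 3 | 5.7% |
| 10% / 20% | 0.5 | 5 | 6.8% |
| 10% / 20% | 0.7 | 7 | 8.4% |
| 5% / 25% | 0.3 | 6 | 8.1% |
| 5% / 25% | 0.5 | 10 | 12.2% |
| 5% / 25% | 0.7 | 14 | 19.5% |

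**A true difference of 15 percentage points (65% against 50%, illustrative).**
- Equal 15% drop-out: 0.85 × 15 = 12.75 points.
- 10% eMST, 20% control: 0.65 × 0.90 − 0.50 × 0.80 = 18.5 points.
- 20% eMST, 10% control: 0.65 × 0.80 − 0.50 × 0.90 = 7.0 points.

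The error can run in either direction.

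**Power with equal 15% drop-out and a true mean difference of 5.7 points.** On the mean scale the difference becomes 0.85 × 5.7 = 4.85 points. For the responder test, with normal changes and SD 7.2, a control gain of 0 gives response rates of 21.4% and 50.0%; a gain of 5.7 gives 50.0% and 78.6%. Under the rule (30 per arm, rates multiplied by 0.85) power is about 48–54% over that range of control gain. Analysing the 25 or 26 patients per arm who would be observed gives about 59–64%. The cost attributable to the rule is the gap between these two, not the gap from a trial with no drop-out.

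**The case against.** The sentence is loosely worded and could mean only that the baseline score fills the visits a patient missed. That is possible, but the text says all evaluation points and makes no exception, so an analyst following it would overwrite. Even so, only those who leave after post-testing are affected. For earlier withdrawers nothing is discarded, and the issue is single imputation alone.

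A reader might infer that the rule biases the result whenever drop-out differs by arm. The documents do not support that. As the formula shows, the bias vanishes if withdrawers would not have improved. The Background says that chronic patients may deteriorate and that recovery depends on dose and intensity, so little change after stopping early is not absurd. The condition that withdrawers would have improved to some degree is therefore part of the point.

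Nor do the documents show that drop-out will differ. Both arms have 40 one-hour sessions, a home visit and weekly contact, so the unequal splits above are scenarios. With equal drop-out the rule is conservative for a superiority claim: it dilutes the difference without inflating type I error.

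A reader might also see a contradiction with the sample size, on the view that the step from 26 to 30 assumes that drop-outs leave the analysis. The Sample size section says only that the rate was taken into account, so this is not a stated contradiction. What remains is that adding patients does not undo the dilution.

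Finally, counting withdrawers as not improved is a recognised, prespecified choice for a responder endpoint. That stands for its use as a sensitivity analysis. It does not justify replacing a measured score, or leaving the primary comparison dependent on the balance of drop-out.

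**Conclusion.** The concern holds in a conditional form. The rule is explicit, so it is not a detail left to an analysis plan. As written it discards observed post-intervention scores of late withdrawers and settles the primary result of about 9 of 60 patients by assignment. It biases the comparison if drop-out differs by arm and withdrawers would have improved to some degree. Under the assumptions set out above, the effect on type I error is modest at 10% against 20% drop-out and serious at 5% against 25%. With equal drop-out the harm is loss of power and a shrunken estimate. The direction of the rule's effect is certain only in that each arm's response rate can be lowered and never raised; the net bias between arms cannot be predicted from the article. The correction should be made before the data are analysed.

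**What to change.** Amend the withdrawal sentence in Data analysis to say that every observed score is kept and that a missing-data method applies only to visits actually missed.

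- **Primary responder endpoint:** multiply impute the ARAT score from baseline, arm and any observed follow-up score. Dichotomise each completed data set at 5.7 points, then compare the arms and pool. This keeps the planned endpoint. A linear mixed model on the ARAT score would change the primary variable and is not needed here.
- **Repeated secondary outcomes:** a likelihood-based mixed model, or multiple imputation followed by the planned ANCOVA.
- **Sensitivity analysis:** keep the baseline-carried-forward rule, applied to missed visits, and report withdrawals by arm and timing alongside the reasons already planned.

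The cost is a change of text, slightly more analysis work, a pooled test in place of a single chi-square, and reliance on a missing-at-random assumption, which the sensitivity analysis helps to probe. No change to recruitment or visits is needed.

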### Evaluation

An initial evaluation will include the collection of demographical and clinical variables will be performed at baseline. In addition, primary and secondary motor, cognitive and emotional well-being and quality of life outcomes will be evaluated before and after the intervention as well as at 3-month follow-up. Table 4 summarises the variables and outcomes of the study. Considering the current health crisis due to the COVID-19 pandemic, the evaluation will be carried out at the participant’s home in order to avoid unnecessary visits to the hospital.

**Table 4 Tab4:** Variables and outcomes of the study

Instrument	Reference	Baseline	Post-intervention	Follow-up

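### The primary analysis reduces the ARAT to improved or not at 5.7 points, tests it with an unadjusted chi-square, and does not say which of two visits decides the trial

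*Protocol article*

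**What the plan says.** The Primary outcome section describes the ARAT as 19 items, each on a 4-point ordinal scale: "The maximum possible score is 57 and the minimal clinically important difference is 5.7 points". Under Evaluation, primary and secondary outcomes "will be evaluated before and after the intervention as well as at 3-month follow-up", and Table 4 marks the ARAT at all three points.

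The Data analysis section then states: "The effect of the intervention on the primary outcome, the ARAT, will be assessed using the chi-square test". It continues: "Taking into account the minimal clinically important difference of this test (5.7 points) data will be dichotomized into two categories", namely improved versus unchanged or worse. No covariate is named for this test. The next sentence treats the other outcomes differently: "An analysis of covariance (ANCOVA) will be carried out for all secondary outcomes to determine differences between groups across time", with demographic and clinical baseline variables as covariates. The section closes with a 5% significance level for all tests and a promise to correct for multiple comparisons where needed.

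The Sample size section refers to a "clinically relevant difference between treatment groups with 80% power and a 5% significance level". It cites 5.7 points as the minimal detectable change and adds that "an acceptable difference between groups of 15% is defined to be clinically meaningful". It arrives at 26 per group, raised to 30 for 15% dropout. It gives neither an SD nor responder rates. None of these sections says whether the post-intervention or the 3-month visit defines improvement.

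**The concern.** The hypothesis is that eMST produces larger improvements than GRASP, which is a question about size of change. The primary test sees only which side of 5.7 points a patient falls on. A gain of 5 and a loss of 10 count the same, and so do gains of 6 and 30. Because the ARAT is scored in whole points, the cut operates as 6 or more. A patient who starts at 52 or above has at most 57 − 52 = 5 points to gain and can never be a responder. The eligibility criteria set no upper ARAT limit.

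Two things are at stake. With 60 patients, a less efficient primary test makes it more likely that a real benefit is missed, and it yields no mean difference to set against the 5.7-point threshold. And with two post-baseline assessments and no named visit, either could be presented as the primary result.

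**Working it through.** **Inputs from the article.** Cut 5.7 points; ARAT maximum 57; 80% power; 5% level (taken as two-sided, since sidedness is not stated); 26 per arm before dropout and 30 after; 15% dropout; withdrawals given their baseline score at every visit.

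**Inputs assumed.** Normally distributed change; a true mean difference of 5.7 points; SD of change 7.2, varied to 5 and 10; control mean gain 3, varied over 0, 2 and 5.

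**1. The plan's own figure.** For a comparison of means, n = 2·SD²·(1.960 + 0.842)²/δ². Solving for the SD that gives n = 26 at δ = 5.7: SD = 5.7 × √13 / 2.802 = 7.34. With the t distribution the value is about 7.2. So 26 per arm can be matched to a comparison of means, but only with an SD that the article does not state. If the 15% is read as a difference in responder proportions, the planned chi-square needs between 48 (0% v 15%) and 174 (42.5% v 57.5%) per arm. The stated basis therefore does not settle which SD applies, which is why a range is used below.

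**2. Information lost by the cut.** For a normal variable, the efficiency of a dichotomised comparison relative to means is φ(c)²/[p(1 − p)], where p is the responder rate and c its normal quantile.

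| Responder rate | Efficiency | Loss |
|---|---|---|
| 50% | 0.637 (= 2/π) | 36% |
| 40% | 0.622 | 38% |
| 30% | 0.576 | 42% |
| 20% | 0.490 | 51% |

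The loss is smallest at 50%, so 36% is the best case.

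**3. Power with SD 7.2.** With control mean gain 3, the eMST mean gain is 3 + 5.7 = 8.7. Responder rates are 1 − Φ((5.7 − 3)/7.2) = 35.4% and 1 − Φ((5.7 − 8.7)/7.2) = 66.2%.

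- At 26 per arm: chi-square 59%, t-test 80%.
- At 30 per arm: chi-square 68%, t-test 85%. Over control gains of 0 to 5 the chi-square figure runs from 64% to 69%.
- For 80% power the chi-square needs about 41 per arm, and 26/41 = 0.63, in line with step 2.

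**4. Dropout handled as planned.** With 15% of each arm set to baseline, responder rates become 0.85 × 35.4% = 30.1% and 0.85 × 66.2% = 56.3%. At 30 per arm, chi-square power is about 54%. A t-test under the same rule, by simulation, has about 75%.

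**5. Sensitivity to the SD, 30 per arm, no dropout.**

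| SD of change | Chi-square | t-test |
|---|---|---|
| 5 | 90–94% | 99% |
| 7.2 | 64–69% | 85% |
| 10 | 40–42% | 58% |

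**6. Whole-point scores with a ceiling at 57.** Simulation at 30 per arm with an assumed baseline SD of 12, change SD of 7.34 and shift of 5.7 compared the chi-square with ANCOVA on baseline ARAT. At a baseline mean of 30, power was 62–64% v 81–82%. At a baseline mean of 40, where the ceiling bites, it was 49–50% v 74–76%.

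**7. Two visits.** If both visits were tested at an uncorrected two-sided 5% and either could count as success, the bivariate normal type I error is 9.1%, 8.3% and 7.0% for correlations of 0.5, 0.7 and 0.9.

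**The case against.** A prespecified responder endpoint at a cited minimal clinically important difference is legitimate. The cut itself introduces no bias, clinicians understand it, and treating gains of 6 and 30 alike is what such an endpoint means. This stands as a reason to keep the responder proportion. It does not make it a good sole primary test with 60 patients.

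Improvement implies change from baseline, so baseline is used, though not as a covariate. Nor does the text say that the secondary ANCOVA adjusts for each outcome's own baseline value. Both remarks are right, and the contrast with the secondary outcomes should be put no more strongly than that.

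The power figures depend on an SD back-solved from the stated 26 per arm. That also stands: the absolute loss varies widely with the SD, although its direction does not change for SDs from 5 to 10. The efficiency figure assumes normal changes, while the ARAT is a bounded sum of ordinal items.

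Three stronger readings are tempting but unsupported. First, a reader might infer that the false-positive rate is inflated. The Data analysis section promises correction where needed, so inflation is possible but not shown; what is missing is whether that promise covers the two ARAT visits. Second, a reader might set the 54% power under dropout against the planned 80%. Baseline carry-forward weakens a comparison of means too, so the like-for-like figure is 75%. Third, a reader might say that the cut discards most of the information. In the best case it is a little over a third, and it reaches about half only at responder rates near 20%.

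Finally, the visit might be named in an analysis plan that is not at hand. But it is part of the definition of the primary outcome, and the article gives the test and the cut-off without it.

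**Conclusion.** The point holds. The article fixes a chi-square without covariates on a dichotomised ARAT as the primary analysis and leaves the deciding visit open between post-intervention and 3 months. The information loss is at least about 36% under a normal model. If the true difference is 5.7 points and the SD 7.2, power falls by roughly 16 to 21 percentage points at 30 per arm (85% to 64–69%), and by about the same with 15% of patients set to baseline (75% to 54%). The loss is smaller at SD 5 and leaves power very low at SD 10. All of these power figures rest on assumed SDs, because the article states none. The multiplicity consequence is conditional: 7–9% applies only if both visits are tested uncorrected.

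**What to change.** - Make the primary analysis a comparison of ARAT score at the post-intervention visit, adjusted for baseline ARAT, by ANCOVA or by a linear mixed model with baseline ARAT, arm, visit and arm-by-visit. Report the mean difference and 95% CI against 5.7 points.
- Name post-intervention as the primary visit and 3 months as secondary.
- Keep the proportion improving by 5.7 points as a supporting analysis.
- Rewrite the Sample size section to match this analysis, with the SD stated and sourced.

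No new assessments or patients are required by the change of analysis itself. The cost is that the headline result becomes a mean difference with the responder rate in support, and that the sample-size basis and the registry entry must be reworded.
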